### Outcome measurements

#### Primary outcome

The primary analysis will compare length in days of non-elective hospital admissions after the index admission during 12 months of follow up between intervention and control conditions. Electronic medical records for each participant will be reviewed at 3 months and 12 months for non-elective public readmissions at hospitals within the included local health district. Private hospital readmissions are not available on the public electronic medical records, therefore will be determined by participant self-report to a blinded outcome assessor at 3 months and 12 months. Reason for readmission will also be gained from electronic medical record and participant self-report, to determine Diagnostic Related Groups (DRGs).

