#### Additional measures

Participants will be asked to self-report their weight and current medications at 3- and 12-month outcome assessments. Current medications will be cross-checked through participant’s pharmacists and Home Medicine Review report where available. Covariables to be considered will include age, sex, degree of frailty at index admission, number of hospitalisations in the preceding 12 months, cognition (MMSE score), and primary admission diagnosis for the index admission and for readmissions.

The hybrid nature of this trial allows understanding of both effectiveness and implementation. Figure 2 describes the conceptual model of evaluation [28]. A process evaluation will be conducted concurrently to describe the adaptation, scale and spread of FORTRESS intervention and details will be described in a separate paper. Details are available through the trial registry.

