### Statistical analysis

The primary analysis will compare length of stay in hospital at readmission after the index hospital admission during 12 months of follow up between intervention and control conditions, using generalised linear mixed models with a negative binomial distribution, accounting for clustering by wards and adjusting for credible confounders to further control baseline imbalance. The approach will be intention to treat.

Secondary analyses will compare time to event of readmission between intervention and control conditions using survival analysis, and frailty status, quality of life outcomes and readmission rates using linear mixed models, accounting for clustering by ward and adjusting for credible confounders.

Covariables to be considered in these analyses will include age, sex, degree of frailty at index admission, number of hospitalisations in the preceding 12 months, cognition (MMSE score), and primary admission diagnosis for the index admission and for readmissions. SAS and R statistical software will be used for analysis.

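### The candidate covariables include the diagnosis at readmission, a post-allocation variable that only readmitted participants have; if used, it would confine the comparison to the readmitted

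*Protocol article*

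**What the plan says.** In the protocol article, the Statistical analysis section sets out the primary model, "generalised linear mixed models with a negative binomial distribution, accounting for clustering by wards", then the secondary analyses, and then gives one list for both: "Covariables to be considered in these analyses will include age, sex, degree of frailty at index admission", ending with "primary admission diagnosis for the index admission and for readmissions". The Additional measures section carries the same list, opening "Covariables to be considered will include age, sex, degree of frailty at index admission".

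The purpose of adjustment in the primary model is given as "adjusting for credible confounders to further control baseline imbalance", and the section adds: "The approach will be intention to treat".

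The Primary outcome section defines the outcome as "length in days of non-elective hospital admissions after the index admission during 12 months of follow up". It collects the diagnosis in question during that same follow-up, from the same sources: "Reason for readmission will also be gained from electronic medical record and participant self-report", in order to assign diagnosis-related groups. Nothing in the article limits the readmission diagnosis to description or costing, or says how a participant with no readmission would be coded.

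**The concern.** Every other item on the list is known at the index admission. The readmission diagnosis is not. It arises after the ward phase has determined what care the participant receives, so it cannot confound the effect of ward phase, and the intervention may itself change it. It is also tied to the outcome: a person has a value only if readmitted, which is to say only if the primary outcome can exceed zero. Someone readmitted several times may have several values.

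If the variable went into the primary model, the benefit that works by keeping people out of hospital would be adjusted away. What remained would be a comparison within a group selected after allocation. The Discussion of the abstract and the Economic analysis both treat avoiding readmission as something the trial is meant to detect.

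**Working it through.** **Inputs**
- Planned effect: 50 days (control) and 35 days (intervention), from Sample size. The ratio is 35/50 = 0.70. I take these as means over all participants, with zero for anyone not readmitted.
- Readmission frequency: about 25% within three months, from the Discussion. This is a background figure for older people, not a planning value for this trial.
- 12-month readmission proportion: not given. A constant hazard would give 1 − 0.75^4 = 0.684. This is an assumption, so 60% and 80% are also shown.
- The enrolment of 732 cannot be reproduced, because no standard deviation is stated (back-solving implies about 49 to 50 days). Nothing below depends on it.

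**Step 1: what a model does with the variable.** A participant never readmitted has zero days and no readmission diagnosis. If the blank is treated as missing, the participant leaves the model. If it is coded as none, that category predicts zero days exactly and contributes nothing to the treatment estimate. Either way the estimate comes from the readmitted. Under the assumed control proportions, 20% (at 80%), 32% (at 68.4%) or 40% (at 60%) of controls would stop contributing.

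**Step 2: formula.** Let p be the proportion readmitted and m the mean days among the readmitted (0 = control, 1 = intervention). Mean days overall are p × m.
- Overall ratio: R = (p1 × m1)/(p0 × m0)
- Conditioned ratio: C = m1/m0 = R × p0/p1

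**Step 3: numbers.** With p0 = 0.684, m0 = 50/0.684 = 73.1 days. Hold R at 0.70, so m1 = 35/p1.

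| p1 | m1 (days) | C = m1/73.1 | Pathway |
|---|---|---|---|
| 0.684 | 51.2 | 0.70 | all through days among the readmitted |
| 0.479 | 73.1 | 1.00 | all through fewer people readmitted |
| 0.40 | 87.5 | 1.20 | fewer readmitted, more days each |
| 0.80 | 43.8 | 0.60 | more readmitted, fewer days each |

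**Step 4: range for p0.** C depends only on R and p0/p1, so the first two rows do not depend on the assumed control proportion. At p0 = 0.60 (83.3 days each), an effect wholly through fewer readmitted needs p1 = 0.42; at p0 = 0.80 (62.5 days each) it needs p1 = 0.56. C is 1.00 in both.

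**Step 5: simulation.** Ten data sets of 20,000 participants per setting were analysed by negative binomial regression, with assumed dispersion 1, no ward clustering, and control proportions of 60% and 80% (the third case at 80% only). A severity factor raised both the chance of readmission and the days.

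| Effect works through | Ratio without the diagnosis | Ratio with it |
|---|---|---|
| fewer people readmitted | 0.73 to 0.74 | 1.04 to 1.06 |
| both, equally on the log scale | 0.72 | 0.86 |
| days among the readmitted | 0.69 | 0.69 |

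Dropping the non-readmitted and coding them as none gave the same estimate. In the first case the conditioned ratio exceeds 1.00 because those still readmitted under the intervention are the more severe.

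**Step 6: secondary analyses.** For time to readmission and readmission rates, having a value is the event itself. For frailty and quality of life the variable is still post-allocation and blank for the non-readmitted, but it does not determine the outcome, and no size is claimed there.

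**The case against.** The strongest reply is that this is a list of candidates. A diagnosis made at readmission fails the article's own test of a credible confounder used to control baseline imbalance, so a statistician applying that test would leave it out. The final adjustment set is commonly fixed in a statistical analysis plan, which is not at hand. This stands to the extent that the consequence is conditional. A reader might infer that the primary estimate will be biased; the documents do not support that, because they do not commit to including the variable. The reply does not remove the defect: the article names the variable, in two places, for analyses that include the primary one, and this conflicts with its own stated purpose and with intention to treat.

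A second reply is that the diagnosis is meant for costing. The Primary outcome and Economic analysis sections already provide for diagnosis-related groups, while the Statistical analysis section lists the diagnosis separately as a covariable for the comparisons.

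A third reply is that the numbers are assumed, which is correct. The 68% extrapolates a background figure and should not be read as the expected proportion in this population. Nor should a reader infer that a conditioned ratio must lie between 0.70 and 1.00: that holds only when the two pathways do not oppose each other, as the 1.20 and 0.60 rows show. The 1.00 result is the case in which the whole benefit comes through fewer people readmitted, and there is no distortion if the chance of readmission is unchanged.

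**Conclusion.** The point holds as an error in the covariable list. A variable that arises after allocation, and that exists only when there has been a readmission, is named as a candidate for the primary and secondary models, against the article's own aim for adjustment.

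The harm depends on two things: that the variable is actually included, and that the intervention alters who is readmitted. Given both, the primary estimate becomes a comparison among the readmitted, equal to the overall ratio multiplied by p0/p1 in the simple calculation. With a true ratio of 0.70 this gave 0.70 to 1.00 when the pathways did not conflict, and 0.60 or 1.20 in the opposing examples, so it can hide a benefit or exaggerate one. These figures rest on assumed readmission proportions and, in the simulation, on an assumed dispersion and no ward clustering. The defect itself does not rest on them.

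**What to change.** In both the Statistical analysis and Additional measures sections, delete the last three words of "primary admission diagnosis for the index admission and for readmissions", so that the item ends with the index admission. Patient-level adjustment then uses only variables known at the index admission. Use readmission diagnoses to describe the readmissions and to cost them by diagnosis-related group, and nowhere in the treatment comparisons.

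The change should stop there. It should not be turned into a closed list of patient variables, because design terms such as ward, site and period belong in a stepped-wedge analysis and are unaffected. If the full protocol or analysis plan repeats the list, the same deletion applies.

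The cost is a wording change. It needs no further data and no change to the sample size, and the diagnoses are still collected.

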### Randomisation procedure

Transition to the intervention phase will be randomised by ward with stratification by site and using minimisation with a random component to optimise baseline and sequential balance. To do this the minimisation algorithm will use anticipated ward characteristics including the type of ward, typical length of stay, high or low tendency to discharge to a day rehabilitation ward rather than home and, where possible, typical readmission rates at that ward.

### Implementation evaluation

Implementation strategies were informed based on consideration of the Consolidated Framework for Implementation Research (CFIR). The CFIR consists of 40 constructs organised into 5 domains: Intervention Characteristics, Outer Setting, Inner Setting, Characteristics of Individuals, and Process [21]. Implementation facilitation on the wards (during the intervention phase) include staff (employed by the research team) facilitating frailty screening and frailty management plans, multiple education sessions for multi-disciplinary team members, signage and documentation (journey board), and posters within the ward to increase awareness. Implementation facilitation has been shown to enhance uptake and sustainability of evidence based practice [29]. Implementation Facilitation will be evaluated through mixed methods including interviews and assessing levels of engagement. Fidelity to the intervention will be measured by the Community Implementation Facilitator reporting adherence to frailty recommendations and motivation of participants in a checklist. Interviews with hospital staff, study participants and their carers will be conducted following hospital discharge. A process evaluation of implementation strategies will be conducted concurrently to FORTRESS intervention with details to be described in a separate paper.

### Economic analysis

The total cost of delivering the intervention will be assessed, and cost-effectiveness analyses will be conducted, according to the principles for conducting economic evaluation alongside stepped wedge trials [30]. The economic evaluation will take the perspective of the health care funder and will include analyses for health outcomes measured in terms of the main clinical outcomes, including cost per extra person avoiding readmission, cost per extra person avoiding frailty, and cost per quality adjusted life years (QALY) gained based on the EQ-5D-5L. The study will collect data on the cost to deliver the intervention (including staff costs, training, capital costs and consumables), and inpatient hospital admissions, based on DRG-related costs. Using the mean costs in each trial arm, and the mean health outcomes in each arm, the incremental cost per extra person avoiding frailty, per extra person avoiding re-admission and per QALY gained of the intervention group compared with control group will be calculated; results will be plotted on a cost-effectiveness plane. Bootstrapping will be used to estimate a distribution around costs and health outcomes, and to calculate the confidence intervals around the incremental cost-effectiveness ratios. One-way sensitivity analysis will be conducted around key variables. A probabilistic sensitivity analysis will be conducted to estimate the joint uncertainty in all parameters, and a cost-effectiveness acceptability curve (CEAC) will be plotted.

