### Intervention

Patients admitted to the wards taking part in this study are screened for eligibility. Baseline frailty is measured using the FRAIL scale [8] and a score of 3 and above indicates frailty. If the person has been admitted to a ward during the control phase of the research study, they will receive usual care as provided by the ward staff and their general practitioner and other health service providers. Participants admitted to the ward during the intervention phase will receive an individualised intervention designed to treat the identified components of frailty, along with the community implementation visit(s), telephone calls, and support from their general practitioner (GP) once discharged. Additional file 1 outlines the TIDier framework [26] describing the FORTRESS intervention. Intervention is divided into two phases:

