#### The Hospital Intervention

Intervention participants will receive referrals for physiotherapy, dietitian and pharmacy review. A tailored Frailty Management Plan will be developed by the multidisciplinary team and documented in the electronic medical record. A tailored exercise program involving resistive training prescribed by the physiotherapist and/or exercise physiologist. Malnutrition screening, nutrition education and advice will be provided by the dietitian. When indicated, the pharmacist will undertake medication history and review at hospital admission and medication reconciliation at discharge, provide education on medication changes and prepare a medication management plan. Indicators for pharmacy review include those experiencing frailty side effects of medication and polypharmacy. The pharmacist will document in the Frailty Management Plan any changes in medication regimen in hospital and the reasons for change; and recommend referral for a Home Medicines Review to be completed within 3 months of discharge. Other frailty interventions such as commencing Vitamin D supplementation may occur when indicated by the medical team or pharmacist. Prior to discharge from hospital, the Frailty Management Plan will be discussed with the participant and/or their significant other who will also receive a copy. Any nutrition and/or exercise recommendations will be detailed and provided in a handout for participants. A copy of the Frailty Management Plan will be sent via fax or secured electronic messaging to the participant’s GP along with all other relevant discharge information.

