#### The Community Intervention

A health professional employed as a Community Implementation Facilitator will review the participant’s motivation and adherence to the Frailty Management Plan recommendations after discharge from hospital and will liaise with the person’s general practice to facilitate ongoing frailty management. The participant will receive a home visit from the Community Implementation Facilitator within a week of discharge, and 2–4 telephone calls in the subsequent 4–6 weeks post discharge. The role of the visits and telephone calls are to support adherence to frailty management plan recommendations, including:Clarify the purposes of the study and answer any questions that the participant or their carer/significant other may have, that have arisen since the participant’s dischargeEnsure study participants understand and can perform the prescribed exercises in their home environmentEncourage study participants to continue with the nutrition interventions at homeAssist/encourage participants to make an appointment to see their GP as soon as practicable following dischargeContact the GP or Practice Nurse with suggested ongoing management of the participant’s Frailty Management Plan

The pharmacist will telephone participants post-discharge to provide detailed education on current medications and recent hospital medication changes. The pharmacy telephone call will entail education to the participant about their medications and encourage them to adhere to the medication management plan prepared in hospital. The Home Medicines Review will be recommended to be initiated by the GP to ensure any medication changes will be implemented by the GP. The Home Medicines Review report will be sent to the participant’s GP, and the study coordinator where available.

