#### Secondary outcomes

Frailty status at baseline, 3 months and 12 months measured using the FRAIL Scale [8].Quality of life at baseline, 3 months and 12 months measured using the EQ-5D-5L [27].Time-to-event of readmission, and readmission rates at 3 months and 12 months.

Baseline measures are assessed by the study Implementation Clinician on the ward at admission. Follow-up outcome assessment will take place via telephone at 3 and 12 months by a health professional masked to group allocation. Each assessment will include administration of the FRAIL Scale to measure frailty and EQ-5D-5L to measure quality of life. Data regarding overnight non-elective hospital readmissions will be obtained from participant self-report, and from public hospital electronic medical records for hospital readmissions.

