## Discussion

Frailty is associated with poorer outcomes for individuals and prevalence is likely to increase due to an ageing population. There is evidence that intervention can effectively reverse frailty and Asia Pacific Guidelines recommend screening and multidisciplinary intervention [16, 22, 23]. This study investigates the efficacy of implementing frailty guidelines for hospitalised older adults and explores the process of implementation in this setting. The results will provide important information which can be used by health care policy makers, managers and clinicians worldwide.

Frail older people with chronic and complex health conditions have high re-admission rates with approximately 25% of older people being readmitted within three months of hospital discharge [31]. Continuity and integration of care following discharge from the acute setting is consistently recommended but difficult to achieve given the current divide between funding for acute and primary care settings. The FORTRESS study aims to work across settings to address frailty identified in a hospital environment. Evidence for cost-effectiveness of preventive, integrated care is generally limited due to a wide variety in study populations, interventions and evaluations [32]. However, previous studies have demonstrated that a multicomponent interdisciplinary frailty intervention is both more effective and less costly than usual care [24]. The FORTRESS study aims to demonstrate that the cost of delivering the intervention will be significantly outweighed by the cost of hospital re-admissions.

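### The economic evaluation does not say which health care funder it means, and its listed costs omit the GP contacts and Home Medicines Reviews that the intervention prompts

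*Protocol article*

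**What the plan says.** On perspective, the Economic analysis section states: "The economic evaluation will take the perspective of the health care funder". The funder is not identified further.

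On costs, the same section states: "The study will collect data on the cost to deliver the intervention (including staff costs, training, capital costs and consumables), and inpatient hospital admissions", with admissions priced from DRGs. Three incremental ratios follow: per additional person not readmitted, per additional person not frail, and per QALY.

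On what the intervention sets in motion, the Intervention section includes among the things intervention participants receive "support from their general practitioner (GP) once discharged". Under The Hospital Intervention, the pharmacist is to "recommend referral for a Home Medicines Review to be completed within 3 months of discharge". Under The Community Intervention, the facilitator encourages an early GP appointment and sends the practice suggestions for continuing management, and "The Home Medicines Review will be recommended to be initiated by the GP".

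On follow-up data, the Secondary outcomes section states: "Each assessment will include administration of the FRAIL Scale to measure frailty and EQ-5D-5L to measure quality of life", alongside readmissions. The Additional measures section adds: "Participants will be asked to self-report their weight and current medications at 3- and 12-month outcome assessments". The Discussion remarks on the "current divide between funding for acute and primary care settings" and sets out to show that readmission costs exceed the cost of delivery.

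**The concern.** A stated perspective fixes which costs belong in the numerator of a cost-effectiveness ratio. Here the list holds programme inputs and inpatient stays. The intervention is designed to hand frailty management to general practice after discharge, and controls get no such prompt. A funder that pays for both hospital and primary care would bear the extra consultations and medicines reviews, but the listed costs would not show them.

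At stake is what the trial can claim in economic terms. The Discussion's comparison sets delivery cost against readmission cost. Prompted primary care appears on neither side, so a finding of cost saving could partly reflect cost moved from one budget to another. The primary clinical analysis is not affected.

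**Working it through.** The article gives no figure to reproduce: it has no unit price for a GP visit or Home Medicines Review, no uptake, no bed-day cost and no delivery cost. The check is a comparison of sections, followed by an illustration of scale.

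**Step 1: trace each cost from the article's own description.**

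| Resource | Prompted by the intervention? | On the cost list? | Measured in both conditions? |
|---|---|---|---|
| Research-employed staff, training, equipment | Yes | Yes | Intervention only, as expected |
| Inpatient readmissions | Meant to fall | Yes | Yes (records and self-report) |
| GP contacts after discharge | Yes | Not named | No item described |
| Home Medicines Review | Yes | Not named | Reports reach the coordinator only where available; stated use is to cross-check medicines |
| Other out-of-hospital care | Unknown | Not named | No item described |

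**Step 2: write the incremental cost.** Let D be delivery cost, S the inpatient saving, P the extra cost of prompted GP contacts and Home Medicines Reviews, and O the difference between conditions in all other out-of-hospital cost, each per intervention participant.

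- Planned: D − S
- For a funder covering all care: D − S + P + O
- Difference: P + O

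P is expected to be positive, because only intervention participants are prompted. It is the increment over control use, since controls also see their GPs. O has unknown sign: if the intervention reduces other community care, O is negative. So the sign of P follows from the article, and the sign of P + O does not. The same numerator feeds all three ratios.

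**Step 3: scale, on assumed values.** Express P in bed-day equivalents, c, and let d be the bed-days saved. The share of the inpatient saving offset is c / d. The Sample size section plans 50 − 35 = 15 days. The range c = 0.1 to 2 is an assumption, as are the smaller values of d.

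| Days saved (d) | c = 0.1 | c = 0.5 | c = 1 | c = 2 |
|---|---|---|---|---|
| 15 (planned) | 0.7% | 3.3% | 6.7% | 13.3% |
| 5 | 2.0% | 10.0% | 20.0% | 40.0% |
| 2 | 5.0% | 25.0% | 50.0% | 100.0% |

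For example, 2 / 15 = 13.3% and 2 / 2 = 100%. These are shares of the gross inpatient saving. The share of the saving net of D would be larger, but the article gives no value for D. Bed-days are only a convenient unit, since the plan prices admissions by DRG.

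**The case against.** The strongest reply is that this is a one-paragraph summary in a journal article. Item-level costing usually sits in a health economic plan, the bracketed delivery items are introduced as inclusions and need not be exhaustive, and GP support is itself described as part of the intervention. That has some force, and the article does not prove that these services will go uncosted. But the article is not merely silent: it states a perspective, the costs to be collected and the content of follow-up, and these fit together only under a narrow reading of the funder. The bracketed items describe programme inputs, and ongoing GP care does not sit naturally among them. The planned one-way and probabilistic sensitivity analyses have no described primary care data to draw on.

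A second reply is that the funder may be the hospital or acute-care funder, in which case the cost list fits. This stands as a possibility. The remaining fault is then that the funder is undefined, in an article that itself notes the funding divide.

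A reader might go further and infer that the evaluation is biased in favour of the intervention. The article does not support that. The direction is clear for the prompted services alone. All other out-of-hospital care is also unlisted in both conditions, and a reduction there would work the other way. Nor can a total in dollars be given, because unit prices, uptake and the split between conditions are not stated, and a Home Medicines Review is recommended rather than guaranteed.

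**Conclusion.** The point holds in a limited form. The perspective and the listed costs do not match if the funder includes primary care. In that case, the cost of GP contacts and Home Medicines Reviews prompted by the intervention is left out of all three ratios, and no described data source would supply it for both conditions. If the funder is the hospital funder only, the costs fit, but the perspective needs saying and the cost-saving claim needs the same limit.

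Neither the net bias nor its size can be determined. On the assumed range, the omission is likely to be small if the planned 15-day saving occurs and could decide the conclusion if the saving is only a day or two. It would be wrong to conclude from this that the economic result favours the intervention overall. The matter is confined to the economic evaluation and is worth correcting there.

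**What to change.** State which funder is meant, then take one of two routes.

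1. Restrict the perspective, and any claim of cost saving, to the hospital or acute-care funder. This costs one sentence and narrows the conclusion.
2. Keep a perspective that includes primary care, and cost GP contacts and Home Medicines Reviews in both conditions from a source that covers early control and later intervention participants equally, such as linked claims data. This costs the linkage, and the ratio may be slightly less favourable.

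Adding questions to the 3- and 12-month calls is cheaper, but it brings recall error and a timing problem. In a stepped wedge, controls are recruited disproportionately early. Recruitment was planned from December 2020 (Time frame) over 16 months (Sample size), so on those dates enrolment would end around April 2022, before publication in June 2022. Questions added part-way through follow-up would miss mainly control participants, so capture would differ by condition.

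On either route, add a scenario analysis over a plausible, pre-stated range of extra GP and Home Medicines Review cost per intervention participant, and report the value at which the conclusion changes. This needs no new participant data.

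### Funder-perspective costing covers inpatient admissions in general, but the admission data described are non-elective only, so a shift to planned stays would count as a pure saving

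*Protocol article*

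**What the plan says.** On perspective, the Economic analysis section states: "The economic evaluation will take the perspective of the health care funder". On resource use, it says the study will collect the cost of delivering the intervention "and inpatient hospital admissions, based on DRG-related costs". Nothing there confines the costed admissions to unplanned ones.

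The capture of admissions is described elsewhere. Under Primary outcome, public records are reviewed at 3 and 12 months "for non-elective public readmissions at hospitals within the included local health district". For private stays the source differs: "Private hospital readmissions are not available on the public electronic medical records, therefore will be determined by participant self-report". Under Secondary outcomes the scope is tighter and applies to both sources: "Data regarding overnight non-elective hospital readmissions will be obtained from participant self-report, and from public hospital electronic medical records".

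The Primary outcome section also says that the reason for each readmission, from the record and from self-report, will be used to determine the DRG. The Discussion sets the economic aim of showing that "the cost of delivering the intervention will be significantly outweighed by the cost of hospital re-admissions".

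**The concern.** Non-elective days are a reasonable primary outcome, but a funder pays for planned stays as well. A costing restricted to unplanned stays therefore answers a narrower question than the stated perspective implies.

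The gap matters because it may not be equal in the two conditions. The intervention sends a management plan to the GP, encourages an early GP appointment and adds facilitator liaison with the practice. Closer follow-up of this kind could lead to some problems being handled by a planned admission instead of an emergency one. Each such exchange would remove a cost from the intervention condition and put nothing back, which would flatter the comparison of delivery cost with readmission cost.

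A second, smaller question concerns length of stay. The trial is powered on days, but the DRG is taken from the reason for readmission, and the article does not say whether the cost attached to it varies with the days recorded.

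**Working it through.** The Economic analysis section gives no figure to reproduce, so the first check sets the sections side by side.

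| Section | Admissions in scope |
|---|---|
| Economic analysis | Inpatient admissions, no restriction stated |
| Primary outcome, record review | Non-elective, public, within the local health district |
| Primary outcome, private stays | Self-report at 3 and 12 months |
| Secondary outcomes, both sources | Overnight, non-elective |

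No section describes collecting elective or same-day stays.

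**Effect on the cost difference.** Let N be the mean cost per participant of the stays that are captured and E that of the stays that are not, with subscripts c (control) and i (intervention).

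- True inpatient saving = (N_c + E_c) − (N_i + E_i)
- Recorded saving = N_c − N_i
- Recorded minus true = E_i − E_c

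If uncaptured stays cost the same in both conditions, the difference is unbiased, although total costs are too low. If planned stays replace unplanned ones, E_i exceeds E_c and the saving is overstated. If the intervention also reduces planned stays, the saving is understated. The article gives neither E nor an elective rate, so no figure can be attached.

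**Length of stay.** The inputs are the Sample size section's 50 days (control) and 35 days (intervention). The fall is (50 − 35)/50 = 30%, a ratio of 0.70. Let f be the share of that ratio, on the log scale, that comes from fewer stays; f is assumed, because the article does not give it. Then the ratio of admissions is 0.70^f and the ratio of length of stay is 0.70^(1−f). With one flat cost per stay, the cost falls by 1 − 0.70^f.

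| f (assumed) | Admissions ratio | Length-of-stay ratio | Cost reduction | Share of the 30% shown |
|---|---|---|---|---|
| 0 | 1.000 | 0.700 | 0% | 0% |
| 0.25 | 0.915 | 0.765 | 8.5% | 28% |
| 0.50 | 0.837 | 0.837 | 16.3% | 54% |
| 0.75 | 0.765 | 0.915 | 23.5% | 78% |
| 1 | 0.700 | 1.000 | 30% | 100% |

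The table holds only if the cost is flat within DRG and the DRG mix does not change.

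**The case against.** The best defence on scope is that the Economic analysis sentence is itself a statement of data collection and is unrestricted. The Outcome measurements section may describe capture for the clinical outcomes only, with wider economic extraction left to a fuller document. That reading is possible, which is why the conclusion is conditional. It does not settle the matter. The article does state a scope for the record review and for self-report, that scope is non-elective, and no wider collection is described anywhere. It is also fair to say that the article never mentions planned admissions as an effect of the intervention. Substitution is a plausible mechanism, not a documented one.

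On length of stay, a reader might infer that days saved within a stay cannot reach the economic result, or that recorded days are left out of the costing. The documents do not support this. They neither state nor exclude a length-of-stay adjustment, and the days needed for one are collected as the primary outcome. DRG costing also picks up every admission avoided. If the funder pays per episode, a shorter stay in the same DRG may be no saving to that funder, so DRG costing could suit the perspective. One-way sensitivity analyses on unnamed key variables are planned and could include a bed-day version. These arguments stand, and they reduce this part to a request for clarity.

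**Conclusion.** The mismatch in scope holds: the costed quantity is wider than the admission data described. If costs rest on those data, elective and same-day stays are missing and any move from unplanned to planned care is credited as a full saving. The direction under substitution is clear, but the size is unknown. A number of days or a percentage for the bias would rest on an invented substitution rate.

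The length-of-stay point is secondary. Under a flat cost per DRG, 0% to 100% of the planned 30% fall in days would appear as a saving. A reader might infer that a positive primary result would sit beside no inpatient saving, or that the Discussion's cost aim cannot be tested. The first requires the extreme case in which only the length of stays changes. The second does not follow, because that aim concerns the cost of readmissions and not days.

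The clinical primary outcome and its analysis are unaffected.

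**What to change.** In the record review and the 3- and 12-month calls already planned, capture all inpatient admissions, including same-day stays, with an elective flag and admission and discharge dates. Keep non-elective days as the primary outcome, but cost all admissions. State in the Economic analysis section which admissions are costed. The calls matter most for private stays: those rest on self-report, so elective private stays not asked about at the time may be hard to recover later.

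State whether DRG-related costs vary with length of stay. Add a costing based on recorded days as a pre-specified sensitivity analysis beside the DRG result, with the caveat that bed-day costing tends to overvalue the later days of a stay.

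The cost is a few extra fields, slightly longer calls and one added analysis. The sample size and the primary analysis do not change.
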